#### Secondary outcome

Given that around 95 % of the general population fail to meet the Chief Medical Officer’s physical activity guidelines when measured objectively by accelerometers [60], this study also allows for the 10 % difference in those meeting the current physical activity recommendation to be detected at follow-up based on 1-beta = 0.8, alpha = 0.025. Consistent with the calculation for ambulatory activity, this study has sufficient power (1-beta = 0.8, alpha = 0.025) to measure a 10 minute/day difference in change in the time spent in moderate-to-vigorous intensity physical activity based on previous work undertaken by our group [16].

This study has sufficient (1-beta = 0.8, alpha = 0.025) power to allow for clinically meaningful differences for change in the biochemical measures to be detected in the entire study cohort and after stratification by ethnicity; fasting glucose (0.3 mmol/l), 2-h glucose (1 mmol/l) and HbA_1c_ (0.25 %).

Furthermore assuming a conversion rate to T2DM in the control group of at least 24 % over the course of the entire study (4 years), we will have an 80 % power to detect a 40 % reduction in the relative risk of T2DM in both intervention groups compared to the control group. The estimated conversion rate is at the lower level reported for traditionally defined prediabetes [7, 61]. We anticipate that the inclusion of an HbA_1c_ defined prediabetes in this study will act to marginally lower the conversion rates, whilst the inclusion of a large South Asian group will act to increase the conversion rates.

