## Methods/Design

### Study design

The study comprises two phases: a development and piloting phase of the text-messaging support for pedometer use and a multi-centre randomised controlled trial. The development phase has been submitted for publication elsewhere, while the present article describes the trial phase.

The trial is a multi-centre randomised controlled trial comparing two modes of physical activity intervention with a control condition. The study is designed to adhere to internationally recognised criteria for developing complex interventions [38]. The design of the study and flow of participants is described in Fig. 1. The study is being run across two centres, Leicester and Cambridge, UK. A total of 1308 participants will be recruited, with 66 % (n = 863) recruited from Leicester. The aim is to have at least 25 % (n = 327) of the total cohort from a South Asian ethnic origin to allow for increased generalisability and the ability to stratify results by ethnicity (see Sample Size).

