### Study outcomes

Data collection clinics are run by research nurses in the Leicester Diabetes Centre, the MRC Epidemiology Unit, Cambridge and other local community centres and clinic areas. All staff have been trained in study procedures and data are collected following standardised operating procedures. Written informed consent is obtained from all participants prior to the commencement of data collection. Details of all clinical assessments and outcome measures are provided in Table 4. Participants are sent a letter with details of selected clinical results after each visit, and their results are also sent to their general practitioner.

**Table 4 Tab4:** Participant assessments at each time point

Clinical Assessment	0 months	12 month	48 months
Family history of disease	X	X	X
Medication status	X	X	X
Smoking status	X	X	X
Muscular/skeletal injury	X	X	X
Blood pressure*	X	X	X
Height*	X		X
Weight*	X	X	X
Waist circumference*	X	X	X
Arm and leg length	X		
Body fat percentage	X	X	X
Fasting and 2-hr glucose and insulin (Leicester only)	X	X	X
HbA_1c_*	X	X	X
Lipids*	X	X	X
Urea & Electrolytes*	X	X	X
Liver Function Tests*	X	X	X
7 Day Step Count & Physical Activity (accelerometer)	X	X	X
Recent Physical Activity Questionnaire (RPAQ)	X	X	X
Dietary questions	X	X	X
Brief Illness Perceptions Questionnaire (BIPQ)		X	X
Physical activity self-efficacy	X	X	X
Enactment of techniques (Groups 2 & 3 only)		X	X
EQ-5D; SF-8	X	X	X
Hospital Anxiety and Depression Scale (HADS)	X	X	X
Sleep	X	X	X
Neighbourhood Environment Walkability Survey (NEWS)	X		
Use of health resources	X	X	X

*Results of these assessments are sent to the participant and their primary care physician

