#### Biochemical variables

Standard biomedical outcomes are assessed by venous sampling. These consist of HbA1c, lipid profile (triglycerides, HDL, LDL, total cholesterol), urea and electrolytes (sodium, potassium, urea, creatinine) and liver function tests (albumin, total bilirubin, alkaline phosphatase, alanine transaminase).

At the Leicester site only, participants are assessed for fasting and 2-hour post challenge glucose and insulin levels using an Oral Glucose Tolerance Test (OGTT). The OGTT results will be used to provide greater clinical insight into how the promotion of physical activity affects metabolic health in prediabetes, given 2-hour glucose and insulin levels better reflect peripheral insulin sensitivity. Given that the new WHO guidelines [40] have led to local clinical practice basing diagnosis of T2DM on HbA_1c_ criteria, the routine use of the OGTT has been phased out of primary care. Therefore, in order to comply with local guidelines and to avoid confusing clinical management strategies in recruited practices, OGTT samples taken in Leicester are frozen and will be analysed after the final study visit (48 month) and not form part of a diagnosis of diabetes. The OGTT involves a fasting blood sample being taken from the patient before they are then given a glucose load of 75 g. A second sample is taken 2 hours later. Fasting and 2-hour plasma glucose and insulin samples are taken at each clinical visit and stored in a −80 °C freezer using standardised, stable methodology within the Leicester Diabetes Research Centre.

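### The power stated for fasting and 2-hour glucose refers to the whole cohort and its ethnic strata, but both are measured only at Leicester (863 of 1308)

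*Protocol article*

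**What the plan says.** All statements are in the Protocol article.

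- **Sample size, Secondary outcome.** "This study has sufficient (1-beta = 0.8, alpha = 0.025) power to allow for clinically meaningful differences for change in the biochemical measures" are said "to be detected in the entire study cohort and after stratification by ethnicity; fasting glucose (0.3 mmol/l), 2-h glucose (1 mmol/l"), with HbA1c (0.25%) as the third measure. All three measures are listed under that one description of the population. Leicester is not mentioned.
- **Biochemical variables.** "At the Leicester site only, participants are assessed for fasting and 2-hour post challenge glucose and insulin levels", by oral glucose tolerance test.
- **Table 4 (Study outcomes).** The row reads "Fasting and 2-hr glucose and insulin (Leicester only") and is marked for 0, 12 and 48 months. The HbA1c row has no site restriction.
- **Study design.** "A total of 1308 participants will be recruited, with 66 % (n = 863) recruited from Leicester". On ethnicity: "The aim is to have at least 25 % (n = 327) of the total cohort from a South Asian ethnic origin". The split of South Asian participants between the sites is not given.
- **Data analysis.** Biochemical outcomes follow the primary strategy, which uses participants with complete data in the group to which they were randomised. Multiple imputation is a sensitivity analysis.

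**The concern.** One population description covers three biochemical measures but fits only HbA1c. For fasting and 2-hour glucose, 1308 − 863 = 445 participants (34%) are planned to have no measurement at any visit. A complete-data analysis cannot include them, and imputation is not the main analysis.

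This matters for interpretation. The glucose tolerance test is included to give added insight into metabolic health, and effects within the two ethnic groups are a stated aim. If a Leicester-only glucose comparison turned out null, particularly within an ethnic group, the power statement could be cited as evidence that the comparison was adequately sized. As written, it refers to a different and larger sample.

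**Working it through.** **Inputs from the article.** Total 1308; Leicester 863; South Asian target at least 327; allocation 1:1:1; power 0.80; alpha 0.025; differences of 0.3 mmol/l (fasting) and 1 mmol/l (2-hour). Drop-out of 30% is stated for the primary outcome only; applying it to glucose is an assumption.

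**Step 1: reproduce the plan's own figures.** For two means, n per arm = 2(z₁₋α/₂ + z₁₋β)²(SD/δ)². With two-sided alpha 0.025, z = 2.2414 + 0.8416 = 3.083, and 3.083² = 9.505.

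- Primary outcome, δ = 1000 and SD = 4000: 2 × 9.505 × 16 = 304.2, rounded up to 305; 305/0.7 = 435.7, rounded up to 436. This matches. A one-sided alpha gives 252 and 360, which does not.
- South Asian stratum: 327/3 × 0.7 = 76.3 per arm; detectable difference 3.083 × 4000 × √(2/76.3) ≈ 1997 steps. This matches the stated figure of around 2000.

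The glucose power itself cannot be reproduced, because the article gives no SD for it. The check is therefore run in reverse: what SD of change is the largest that still gives 80% power?

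**Step 2: formulas.** Evaluable per arm m = 0.7 × N/3. Detectable difference in SD units = 3.083 × √(2/m). Largest SD = δ divided by that value.

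| Sample | N | m per arm | Detectable (SD) | Largest SD, fasting 0.3 | Largest SD, 2-hour 1.0 |
|---|---|---|---|---|---|
| Whole cohort | 1308 | 305.2 | 0.250 | 1.20 | 4.01 |
| Leicester | 863 | 201.4 | 0.307 | 0.98 | 3.26 |

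The ratio of detectable differences is √(1308/863) = 1.23. It does not depend on the drop-out rate if that rate is the same at both sites. Without any drop-out the Leicester limits would be 1.17 and 3.89.

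**Step 3: ethnic strata, at the minimum target of 327 South Asians.** The remaining 1308 − 327 = 981 are taken as White European.

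| Stratum with glucose data | N | m per arm | Largest SD, fasting | Largest SD, 2-hour |
|---|---|---|---|---|
| South Asian, both sites (reference) | 327 | 76.3 | 0.60 | 2.00 |
| White European, both sites (reference) | 981 | 228.9 | 1.04 | 3.47 |
| All South Asians at Leicester: South Asian | 327 | 76.3 | 0.60 | 2.00 |
| All South Asians at Leicester: White European | 863 − 327 = 536 | 125.1 | 0.77 | 2.57 |
| Pro rata (assumption): South Asian | 0.25 × 863 ≈ 216 | 50.3 | 0.49 | 1.63 |
| Pro rata (assumption): White European | 0.75 × 863 ≈ 647 | 151.0 | 0.85 | 2.82 |

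The 445 participants without glucose data must come from one stratum or both. If all South Asians are at Leicester, that stratum loses nothing and the White European stratum carries the whole reduction. If recruitment is pro rata, both shrink.

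**The case against.** The strongest reply is that only a label is wrong. The phrase about the cohort stands in contrast to stratification by ethnicity, so it may mean pooled rather than all 1308, and nothing shows that 1308 was the number used. The restriction to Leicester is disclosed twice, these are secondary outcomes, and the power may well be adequate: on Leicester alone 80% is kept overall with SDs up to about 0.98 and 3.26.

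Much of this stands. A reader might infer that the trial is underpowered for glucose, or that power drops to 60%. The second figure comes from Φ(3.083 × √(863/1308) − 2.2414) = 0.60 and holds only if the comparison was sized at exactly 80% on the full number, which the article does not say. Power figures for South Asians from an assumed fasting SD would be no firmer: with all 327 at Leicester, an SD of 0.5 gives 93% and an SD of 0.8 gives 53%, and the article offers no basis for choosing. A reader might also treat 109 South Asians per arm (327/3) as a ceiling, but 327 is a floor. Nor is the absent SD a fault in itself, since a condensed article commonly leaves it to the full protocol.

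What the reply does not remove is the mismatch. Even if the phrase means pooled, the sentence places glucose and HbA1c on the same sample, and two other places in the article show that they are not.

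**Conclusion.** The point holds as an inconsistency about the population to which a power statement applies. It is not a demonstrated shortfall in power. For fasting and 2-hour glucose the relevant sample is Leicester's 863, not 1308. Under the assumed 30% drop-out the detectable difference is 23% wider than the whole-cohort number would give, and the overall claim is true only within the SD limits of about 0.98 and 3.26 mmol/l.

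The claim by ethnicity is the more exposed, because at the target of 327 at least one stratum must be smaller than in the full cohort. Which one, and by how much, depends on a site split that the article does not state. The HbA1c claim is unaffected by the site restriction. The issue is confined to secondary outcomes but is worth correcting, since it bears on how a null glucose result would be read.

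**What to change.** Reword the biochemical paragraph of the sample size section. Keep the whole-cohort power statement for HbA1c only. For fasting and 2-hour glucose, state the power or detectable difference for the Leicester subset (n = 863), overall and by ethnicity, with the number of South Asian and White European participants expected at Leicester and the drop-out assumed for these measures.

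The cost is one paragraph and possibly a less favourable secondary power figure. Recruitment, measurement and analysis stay as they are.

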### Data analysis

Analysis will involve two *a priori* comparisons; both intervention groups will be compared to the control group. Should any of these comparisons reveal a significant difference, then a third *a priori* comparison will be undertaken by comparing the difference between intervention groups - this will be included as a secondary analysis. Multiple linear regression analysis will be used to investigate the differences in the change in physical activity level achieved between groups at 48 months, after adjusting for potential areas of bias between groups, valid accelerometer wear time and the number of valid wear days. Analysis will be conducted on the cohort as a whole and stratified by ethnic group; interaction terms will be used to quantify the effect of ethnic group. We will also use interaction terms to assess whether the effects of the interventions are modified of gender, age, ethnicity, family history of T2DM or whether prediabetes status was confirmed at baseline; significant interactions will followed by stratified analysis. We will also assess change in physical activity at 12 months as a secondary outcome. The primary analysis will be based on analysing those with complete data at each time point in the group to which they were randomised. A sensitivity analysis will be undertaken to assess the impact of imputing missing data through multiple imputation and through a per-protocol analysis by removing those that failed to attend the initial Walking Away session in both intervention groups; per-protocol analysis for the Walking Away Plus group will be defined as removing those that that failed to attend the initial Walking Away session OR those that failed to register for or actively stopped their text messaging support via the STOP function within the first 2 months.

Analysis of secondary biochemical and anthropometric outcomes will be analysed using the same strategy and at the same time-points as that described for the primary outcome. Differentials in the time to T2DM between groups will be plotted using the Kaplan–Meier method for comparing survival curves; the log rank test will be used to assess for differences between the groups.

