Whilst structured education has been identified as a potentially effective method of promoting behaviour change in the prevention of T2DM, guidelines recommend the provision of regular ongoing support [6, 36]. It is essential to develop sustainable and scalable approaches, such as mHealth, to enhance and reinforce the aims of structured education programmes or other face-to-face behaviour change interventions.

Given the above considerations, there is an identified need to develop and evaluate the use of structured education as a tool for promoting health behaviour change in those with prediabetes with tailored, ongoing support through low-resource approaches. Here we test whether the approach used in the PREPARE structured education programme, which has proven efficacy [32, 37], can promote long-term changes to physical activity and whether the programme’s effectiveness is enhanced through the use of a follow-on support programme combining pedometer self-monitoring with tailored text-messaging and telephone calls.

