### Aims and objectives

To investigate whether an intervention to support physical activity change and maintenance, offered to an ethnically diverse population with prediabetes, can lead to sustained increases in physical activity over four years.To investigate the effectiveness of the intervention when delivered at two levels of intensity, with and without follow-on support that enhances self-monitoring with pedometers through tailored text-messaging and telephone calls.To investigate the effect of the intervention within White Europeans and South Asians sub-groups.To conduct a within-trial and long-term economic evaluation of both intervention conditions using the costs and benefits arising from the study, rates of progression to T2DM, biomedical outcomes, NHS resource use, and quality-of-life.

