### Sample size

#### Primary outcome

For 1-beta = 0.8, alpha = 0.025 (allowing for 2 a priori comparisons against control conditions), SD = 4000 steps/day and a drop-out of 30 %, we require 436 per group (1308 in total) to detect a 1000 steps/day difference in change in ambulatory activity (equivalent to 10 mins walking/day or 70 mins walking/week) between the intervention groups and control group. Assuming 25 % of participants in the total cohort are SA we have an 80 % power to detect around a 2000 steps/day difference when comparing two intervention comparisons to the control group (alpha = 0.025) in the SA population.

Several intervention studies with a follow-up of between 3 to 12-months reported a standard deviation of change in ambulatory activity of around 3000 to 4000 steps per day in individuals with T2DM, prediabetes or in sedentary individuals [32, 57–59].Therefore we have anticipated a standard deviation of change of 4000 steps per day. An intervention effect of 1000 steps was considered the minimum clinically significant difference between groups and equates to around a 4 % difference in the risk of cardiovascular morbidity and mortality [13].

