## Discussion

This trial will provide important insight regarding the long term effectiveness and cost-effectiveness of a group-based structured education programme for physical activity targeting those with prediabetes within primary care, and the effectiveness of a highly-tailored and evidence-based text-messaging and telephone follow-on system designed to support ongoing behaviour change and pedometer use. NICE guidelines on diabetes prevention recommend the use of group-based lifestyle intervention for prediabetes as the cornerstone of any diabetes prevention pathway [6], so it is important to investigate the use of structured education within the prevention domain. It is imperative that any intervention programme is carefully evaluated for both clinical and cost-effectiveness, as well as its capacity to be easily implemented into primary care. Whilst both the effectiveness and cost-effectiveness of structured education for those diagnosed with T2DM have already been established [34, 35], and is recommended by NICE as best clinical practice for the management of T2DM [33], there is a lack of translational research within the context of diabetes prevention. Consequently this limits the capacity of commissioners and policy makers to make informed evidence-based decisions regarding the implementation of national diabetes prevention programmes within primary care. Furthermore there is a need to establish what the optimal levels of ongoing support are to ensure any behaviour change is maintained, taking into account the limited resources available in most healthcare settings. This study evaluates highly-tailored, evidence-based text-messaging tool which requires few resources and time, and thus will help address both of these limitations.

The Walking Away from Diabetes structured educational programme and the follow-on text-messaging and telephone support system have been specifically designed to be translated into primary care. This type of lifestyle intervention in prediabetes could be easily added to other programmes currently on offer for the management of type 2 diabetes, thereby allowing a range of structured education packages and evidence-based mHealth interventions to be offered, to best serve the needs of the diabetes pathways within primary care.

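### The direct Walking Away Plus versus Walking Away contrast is reported only if a comparison with control is significant, so the estimate of what follow-on support adds may be withheld, or shown only after selection

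*Protocol article*

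**What the plan says.** The Data analysis section of the protocol article names two a priori comparisons, each intervention arm against control. The comparison between the intervention arms is conditional: "Should any of these comparisons reveal a significant difference, then a third" comparison is made, and "this will be included as a secondary analysis". The section does not provide for estimating that difference when neither control comparison is significant, and no other section does so.

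The question behind the contrast is stated in several places. The Background (Structured education for the prevention of T2DM) says the trial tests whether the programme's "effectiveness is enhanced through the use of a follow-on support programme". The second objective under Aims and objectives is "To investigate the effectiveness of the intervention when delivered at two levels of intensity, with and without follow-on support". The Discussion adds that "there is a need to establish what the optimal levels of ongoing support are".

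The Sample size section (Primary outcome) covers only the comparisons with control: "alpha = 0.025 (allowing for 2 a priori comparisons against control conditions"), with 80% power, 30% drop-out and 436 participants per group. It also states that "we have anticipated a standard deviation of change of 4000 steps per day" and "An intervention effect of 1000 steps was considered the minimum clinically significant difference between groups".

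**The concern.** The two intervention arms differ only in the text-messaging and telephone support, so the randomised contrast between them is the direct measure of what that support adds. A significant result against control is not needed for that contrast to be valid. Making it conditional has two possible consequences.

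- If neither arm is significant against control, the rule as written produces no direct contrast and no interval for it. Readers may then compare two control comparisons by eye, or compare one arm's p-value with the other's, and neither gives the uncertainty of the difference.
- If the contrast is run, it has been selected on a correlated result. Its average over the trials in which it appears can differ from the truth, and its nominal 95% interval need not have 95% coverage.

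The contrast is already labelled secondary, so the gate is not needed to protect the two primary tests.

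**Working it through.** **Step 1. Reproduce the planned sample size.** Inputs from the Sample size section: difference 1000, SD 4000, alpha 0.025, power 0.80, drop-out 30%.

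n per arm = 2 × (z₀.₉₈₇₅ + z₀.₈₀)² × (SD/difference)² = 2 × (2.2414 + 0.8416)² × (4000/1000)² ≈ 304.2, rounded up to 305.

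Allowing for drop-out: 305/0.70 = 435.7, rounded up to 436. This matches the plan. A one-sided 0.025 would give 252, or 360 after drop-out, which does not match, so 0.025 is taken as two-sided.

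**Step 2. Precision of any pairwise contrast at 305 completers per arm.**

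SE = 4000 × √(2/305) = 324 steps/day. The 95% half-width is 1.96 × 324 ≈ 635 steps/day. The gate opens when an observed difference from control exceeds 2.2414 × 324 ≈ 726 steps/day in absolute value.

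**Step 3. Simulate the rule.** Four million trials per scenario, three arm means each with SE 4000/√305 and a shared control. The contrast is run if either control comparison passes the gate. The true effects are assumptions, because the article does not give separate expected effects for the two arms.

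| True effects vs control (Walking Away/Plus) | Not run | True Plus − Walking Away | Mean when run | 95% CI coverage when run |
|---|---|---|---|---|
| 0/0 | 95% | 0 | 0 | 76% |
| 0/500 | 74% | 500 | 707 | 91% |
| 250/500 | 73% | 250 | 382 | 90% |
| 300/800 | 40% | 500 | 593 | 94% |
| 500/500 | 63% | 0 | 0 | 90% |
| 500/1000 | 19% | 500 | 545 | 95% |
| 1000/500 | 19% | −500 | −545 | 95% |
| 1000/1000 | 9% | 0 | 0 | 95% |
| 1000/1500 | 0.6% | 500 | 502 | 95% |

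The 1000/500 row shows that the selection works in both directions: when Walking Away is the better arm, Plus looks worse than it is.

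**Step 4. What the gate hides.** At 0/500 the contrast would be nominally significant at 0.05 in 33.9% of all trials, but it is both run and significant in only 15.6%. In 33.9 − 15.6 = 18.3% of trials such a difference is never examined.

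**Step 5. Sensitivity to the gate level.** The Data analysis section does not define what counts as significant, and 0.025 is taken from the Sample size section. With a gate at two-sided 0.05 the contrast is run in 37%, 71% and 88% of trials at 0/500, 300/800 and 500/1000, with means of about 674, 569 and 530 against a true 500. The pattern is the same and somewhat milder.

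**Step 6. Without the gate.** The contrast is always estimated, is unbiased, and has a 95% interval of about ±635 steps/day with correct coverage. Power at two-sided 0.05 is 34% for a 500-step difference and 87% for 1000 steps.

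**The case against.** The case for the rule has real force on four points.

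- **Gating a test is ordinary hierarchical practice.** Here it holds the unconditional false-positive rate of the third test to 1.1% at 0/0 and 3.5% at 500/500, instead of 5%. This stands. It supports restricting a significance claim, but not withholding an estimate and its interval.
- **The second objective is not left wholly unanswered.** Both control comparisons are always made, and they share a control group and an analysis strategy. A reader might infer that the trial could end with no information on the added value of support. The article does not support that, since a point difference can be taken from the two reported effects. What can be lost is the direct contrast with its confidence interval, because the two control comparisons are correlated and their separate intervals do not give it. The second objective, read literally, could also be met by two comparisons with control; the Background wording on enhancement is what points to the direct contrast.
- **Exaggeration is not general.** A reader might infer that the reported difference is always biased upwards. It is not: signed bias is nil when the arms are equal, runs the other way when Walking Away is better, and is negligible when both effects are at or above 1000 steps.
- **The fixed 0.025 is sound.** A reader might take this point as a criticism of the multiplicity allowance. It is not one: 0.025 for each of two comparisons is valid and reproduces 436 per group.

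**Conclusion.** The point holds as a narrow one about a declared secondary analysis; the primary result is not affected. The stated rule makes the direct estimate of a stated trial question depend on significance elsewhere. The chance that it is not reported runs from 9% when both arms have the planned effect to 74% at 0/500 steps. When it is reported, the mean exaggeration is about 41% at 0/500 (207 of 500) and 9% at 500/1000 (45 of 500). It is nil with equal arms, although conditional interval coverage then falls to about 90% at 500/500 and 76% at 0/0.

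These sizes rest on 305 completers per arm, SD 4000, a normal approximation, a gate at two-sided 0.025 and the assumed true effects. Covariate adjustment and the allocation of household members to the same arm are ignored. The existence of the problem depends only on the wording of the rule; its size depends on effects that are not known in advance.

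**What to change.** In the Data analysis section, replace the conditional sentence with a statement that Walking Away Plus minus Walking Away at 48 months will be estimated and reported with its 95% confidence interval as a pre-specified secondary estimate, whatever the comparisons with control show. If the investigators want to keep hierarchical control, they can add that a confirmatory significance claim for this contrast will be made only if at least one control comparison is significant, and state the level that counts as significant.

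The cost is a sentence or two. No extra participants or data are needed, and the sample size and the two primary tests are unchanged. The interval will be wide relative to the 1000-step minimum important difference (about ±635 steps/day), so the report should present the contrast as an estimate and not read a non-significant result as evidence that the support adds nothing.

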### Randomisation

Once baseline data have been collected, participants are randomised (stratified by sex and ethnicity) using an online randomisation tool hosted at the University of Leicester Clinical Trials Unit. Individuals are randomised (1:1:1) to the control group, the Walking Away Group or the Walking Away Plus Group. The exception to this is individuals recruited from the same household, who are randomised to the same group. Participants are informed of their allocated treatment after baseline measures are completed. Study allocation is concealed from the study measurement teams conducting the 12-month and 48-month follow-up.

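### The primary model for change in steps/day does not name baseline steps or the randomisation strata as covariates and leaves its adjustment set open, so precision available at almost no cost may be lost

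*Protocol article*

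**What the plan says.** All references are to the protocol article.

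- **Data analysis.** The primary analysis is a multiple linear regression of the change in physical activity at 48 months, "after adjusting for potential areas of bias between groups, valid accelerometer wear time and the number of valid wear days". Ethnicity appears through stratified analyses and interaction terms, and gender as a possible effect modifier. Neither is named as a covariate in the main model. The biochemical and anthropometric secondary outcomes follow the same strategy.
- **Study outcomes, Primary outcome, and Table 4.** Steps are measured by accelerometer at baseline, 12 and 48 months. The two wear covariates are justified by possible differences between groups in obtaining valid recordings.
- **Randomisation.** After baseline data collection, "participants are randomised (stratified by sex and ethnicity) using an online randomisation tool".
- **Study design.** "The study is being run across two centres, Leicester and Cambridge, UK". Centre is not listed as a stratification factor, and 66% of participants are to come from Leicester.
- **Sample size, Primary outcome.** The calculation rests on the SD of the change score: "we have anticipated a standard deviation of change of 4000 steps per day". No covariate gain is assumed.

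**The concern.** A change score subtracts the whole baseline value. Unless baseline and follow-up are perfectly correlated, that is too much, and the estimate keeps part of any chance difference in baseline steps between groups. Putting baseline steps in the regression removes that part and reduces the residual variance. Because the change score needs the baseline value anyway, the adjustment asks for no further data.

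Sex and ethnicity were chosen as strata and balanced by design. A model without them counts the variation between strata as noise, which makes its standard errors somewhat too large.

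The open bias term is a separate weakness. It gives no list and no selection rule, so two analysts could follow the sentence faithfully and report different primary estimates. At stake are precision and a primary analysis settled in advance, not the validity of the design.

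**Working it through.** **Inputs from the article** (Sample size, Primary outcome): power 0.80; "alpha = 0.025 (allowing for 2 a priori comparisons against control conditions"); SD of change 4000; difference 1000 ("to detect a 1000 steps/day difference in change in ambulatory activity"); and "a drop-out of 30" per cent. Sidedness is not stated. Two-sided 0.025 reproduces the figure, whereas one-sided 0.025 would give 252 evaluable and 360 recruited per group.

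**Step 1: the plan's own figure.** n = 2 × 4000² × (2.2414 + 0.8416)² / 1000² = 304.2, so 305 evaluable per group. 305 / 0.70 = 435.7, so 436 per group and 1308 in total. This matches "we require 436 per group (1308 in total"). Power at 305 is Φ(1000 / (4000 × √(2/305)) − 2.2414) = Φ(0.846) = 80.1%.

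**Step 2: add baseline steps.** Let ρ be the correlation between baseline and 48-month steps. *Assumption:* the article gives no ρ, so a range is shown, with equal SDs at both times. Then residual variance / change-score variance = (1 + ρ)/2, a reduction of (1 − ρ)/2. The SD of change is held at 4000, so the residual SD is 4000 × √((1 + ρ)/2).

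| Assumed ρ | Variance ratio | Residual SD | Power at 305 per group |
|---|---|---|---|
| change score, no covariate | 1.00 | 4000 | 80.1% |
| 0.5 | 0.75 | 3464 | 90.7% |
| 0.6 | 0.80 | 3578 | 88.7% |
| 0.7 | 0.85 | 3688 | 86.6% |
| 0.8 | 0.90 | 3795 | 84.4% |
| 0.9 | 0.95 | 3899 | 82.3% |

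**Step 3: unequal SDs.** With k = follow-up SD / baseline SD, the ratio is k²(1 − ρ²) / (1 + k² − 2ρk). At k = 1.25 it is 0.89 for ρ = 0.5 and 1.00 (no gain) for ρ = 0.8. At k = 0.8 it is 0.57 and 0.64, a larger gain than with equal SDs.

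**Step 4: chance imbalance.** With equal SDs, the change-score contrast carries −(1 − ρ) times the baseline difference between groups. At ρ = 0.5 an SD of change of 4000 implies a single-time SD of 4000 / √(2 × 0.5) = 4000. One standard error of the baseline difference is 4000 × √(2/305) = 324 steps/day, which moves the estimate by 0.5 × 324 = 162 steps/day against a target of 1000.

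**Step 5: strata and centre.** *Assumption:* sex, ethnicity and centre together explain 1% to 5% of the variance of change. Using SD = 4000 × √(1 − R²) without baseline steps, power is 80.5% to 82.3%, a gain of 0.4 to 2.2 points. Nearly all of the available gain therefore comes from baseline steps.

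**The case against.** The strongest reply is that silence is not exclusion. The bias term is undefined and could include baseline steps, sex, ethnicity and centre. A change score can itself be regressed on baseline. An article commonly leaves the full covariate list to an analysis plan, and the section on the steering and monitoring committees mentions review of analysis plans. This stands in part: the article cannot be said to leave these variables out. But it does print an adjustment set for its primary model, with two named covariates and one open-ended term, and that wording can fairly be criticised.

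Four stronger readings are tempting, and the article does not support them.

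- *Covariates will be picked from observed imbalance.* The article speaks of potential bias and gives no selection rule. The defect is that the set is open, not that it is known to be data-driven.
- *The trial is underpowered.* It is powered on the unadjusted SD of change and takes the top of its cited range of 3000 to 4000.
- *Power falls to 64% with a change score, against 84% with baseline adjustment.* This needs a single-time SD of 4000 and ρ = 0.3, hence an SD of change of 4000 × √1.4 = 4733. Neither input is in the article, and the scenario disputes the planned SD, which is a different question.
- *Adjusting for wear is an error that costs precision.* Follow-up wear is measured after randomisation and might be affected by allocation, but that concerns the estimand and bias. The article gives a reason for the adjustment, and it may even reduce residual variance.

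Two further limits stand. Regression to the mean acts in all randomised groups and does not bias the contrast on average; only chance imbalance remains. Centre was not a stratum, so its case is weaker.

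**Conclusion.** The point holds as a worthwhile improvement at almost no cost, not as an error that undermines the trial. The stated primary model does not name baseline steps/day, sex or ethnicity, and it leaves its adjustment set open. On the planned SD of change, and with equal SDs, adding baseline steps would raise power from 80.1% to between about 82% (ρ = 0.9) and 91% (ρ = 0.5) at the same 305 evaluable participants per group. That range rests on an assumed ρ and shrinks, possibly to nothing, if steps are more variable at 48 months than at baseline. The strata contribute little power; the reason to include them is that the model should match the randomisation. The sample size needs no change on this account.

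**What to change.** In Data analysis, specify the primary model as 48-month steps/day (or change in steps/day) regressed on randomised group, with baseline steps/day, sex and ethnicity as fixed covariates. Centre may be added. Replace the open bias term with this list. Analyse each continuous secondary outcome in the same way with its own baseline value, where one is measured.

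The cost is wording only, to be settled before the data are unblinded. All the variables are already collected. A rule is needed for participants without a valid baseline recording, but the complete-data change score already loses them.

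Optionally, report the primary result with and without follow-up wear time and valid days. Whether these covariates stay in the primary model is a judgement for the trial team and not part of the required change.
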